#### Power analysis

2.1.4

Qualitative sample sizes were selected based on established rapid, framework-guided thematic saturation and feasibility. For Aim 1, 20 SMW/TGD community members distributed across several interviews or focus groups are expected to provide sufficient diversity of perspectives regarding hazardous drinking, posttraumatic stress, treatment experiences, and barriers and facilitators to care [134,135]. For provider interviews, empirical studies suggest thematic saturation commonly occurs within focused samples of approximately 8–12 interviews [136]; therefore, a target of 10 providers is expected to be adequate for eliciting perspectives on intervention feasibility, implementation barriers, and best practices in SMW/TGD-affirming care. For Aim 2, recent methodological guidance discourages using pilot trials to establish efficacy or generate definitive effect size estimates [137]. Accordingly, this pilot trial is designed primarily to estimate feasibility, acceptability, recruitment, retention, adherence, and assessment parameters to inform a future fully powered randomized controlled trial. Consistent with recommendations for behavioral pilot trials [138], we will target enrollment of 60 participants randomized across two conditions (30 per condition). The target sample incorporates anticipated attrition of approximately 20%, based on this study team's prior EW intervention research with a similar population [77] and existing telehealth-delivered CBT and EW studies involving SMW/TGD populations [70,99], while recognizing that attrition may be elevated among populations experiencing substantial psychosocial burden and barriers to care. This sample size is expected to provide sufficiently precise estimates of feasibility and acceptability indicators while supporting preliminary examination of clinical outcome trends.

#### Analytic plan

2.1.5

##### Aim 1

2.1.5.1

Aim 1 qualitative data will be analyzed using a rapid, framework-guided thematic analysis [134,139] informed by ADAPT-ITT domains (e.g., content, format, delivery, safety), treatment targets, and SMW/TGD-specific considerations relevant to intervention adaptation. An initial codebook will be developed deductively from ADAPT-ITT domains, intervention mechanisms, and SMW/TGD-relevant contextual factors, with iterative refinement through team discussion and memoing. Two coders will independently code an initial subset of transcripts to establish coding consistency and refine codes; subsequent coding will include periodic double-coding, consensus meetings, and adjudication procedures to resolve discrepancies.

Data will be synthesized using a framework matrix approach to identify key themes, convergent and divergent perspectives across community members and providers, and implications for intervention refinement [140]. Findings will be translated into an adaptation matrix documenting proposed modifications, supporting evidence, rationale, feasibility considerations, and priority ratings to guide revisions to the RISE manual and study procedures.

To enhance rigor and transparency, the research team will maintain an audit trail of coding and adaptation decisions, as well as versioned intervention updates. Reporting will follow established standards (e.g., consolidated criteria for reporting qualitative research; [141]).

##### Aim 2

2.1.5.2

**Acceptability and Feasibility Analyses.** Qualitative feedback regarding intervention acceptability will undergo rapid, framework-guided thematic analysis using coding, consensus, and synthesis procedures consistent with the Aim 1 analytic approach. Quantitative feasibility and acceptability indicators will be summarized descriptively, including recruitment yield, screening-to-enrollment ratios, intervention uptake and completion, retention, assessment completion, missingness, risk assessments, and participant-reported acceptability measures. Group differences in feasibility indicators may be explored using appropriate descriptive or inferential statistics; however, emphasis will remain on estimation, confidence intervals, and interpretation of implementation parameters rather than hypothesis testing.

**Initial Outcome and Descriptive Trend Analyses**. We will first summarize sample characteristics, evaluate baseline comparability between study arms, and examine patterns of missingness. Baseline variables differing across arms and associated with outcomes may be included as prespecified covariates. Primary clinical outcomes will include hazardous drinking and posttraumatic stress symptom severity, consistent with the intervention's principal clinical targets. Exploratory analyses will examine selected transdiagnostic process measures aligned with the intervention model, including emotion regulation difficulties, experiential avoidance, anxiety sensitivity, negative emotionality, coping strategies, posttraumatic maladaptive beliefs, and alcohol craving, to inform future mechanism-focused trials.

Clinical outcomes will be analyzed using mixed-effects models appropriate to outcome distributions (e.g., linear models for approximately normal outcomes; generalized models for count outcomes). Primary analyses will test the time × treatment arm interaction (immediate vs. waitlist) across assessment timepoints using an intention-to-treat framework [142]. Models will include fixed effects for time, treatment arm, and time × arm interactions, relevant covariates, and participant-level random effects. Sensitivity analyses will examine completer-only models and alternative model specifications as appropriate.

Consistent with recommendations for pilot trials, analyses will emphasize estimation rather than efficacy testing. We will report standardized effect size estimates (e.g., Hedges’ *g*) with 95% confidence intervals, descriptive outcome trajectories, and preliminary clinical trends to inform refinement, feasibility assessment, and planning of a future fully powered randomized controlled trial. No interim efficacy analyses are planned.

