#### Trial design

2.1.1

To address Aim 2, we will conduct a pilot randomized controlled trial using a parallel, 1:1 unstratified allocation design comparing immediate treatment receipt with a 6-week waitlist control condition (see Fig. 1). Consistent with the pilot nature of the study, treatment outcome findings will be interpreted as preliminary estimates intended to inform feasibility, acceptability, and future efficacy testing. Outcome data will be collected through virtual clinician-administered interviews and online self-report assessments. Participants randomized to immediate treatment will complete assessments at baseline, post-treatment (following completion of UP modules and EW sessions), and 1-week follow-up. Participants randomized to the waitlist condition will complete assessments at baseline, post-waitlist (i.e., second baseline/prior to treatment initiation), post-treatment, and 1-week follow-up (see Fig. 1).

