**Immediate condition.** Participants randomized to the immediate condition will begin RISE within 2 weeks following randomization. Participants will be allowed up to 6 weeks to complete the intervention, including four UP-based sessions delivered across five weeks followed by five days of EW completed within 1 week. Participants will also complete post-treatment assessments and a 1-week follow-up assessment. Limited scheduling flexibility (e.g., brief rescheduling, temporary pauses) will be permitted and documented to accommodate participant burden, availability, or clinically indicated needs while maintaining intervention and assessment sequencing.

**Waitlist control condition.** Participants randomized to the waitlist condition will complete baseline assessments identical to those completed by the immediate treatment group and then enter a 6-week wait period. Following the wait period, participants will complete a post-waitlist assessment (i.e., prior-to-treatment assessment) identical to the immediate treatment group's post-treatment assessment. Participants in the waitlist condition will then begin RISE within approximately two weeks of the post-waitlist assessment and will follow the same intervention timeline and assessment schedule as the immediate treatment group, including post-treatment and 1-week follow-up assessments. Providing RISE following the wait period is intended to maintain access to care and support ethical study conduct.

**RISE intervention.** RISE is a brief, telehealth-delivered intervention consisting of four once-weekly adapted UP skill sessions (Modules 2–5) followed by five consecutive days of EW (see Fig. 1). UP sessions will focus on understanding emotions, cultivating mindful emotional awareness, enhancing cognitive flexibility, and countering emotion-driven behaviors in contexts relevant to SMW/TGD people's experiences, such as using alcohol to cope with anticipated stigma, trauma, or difficult emotional states, and relying on avoidance coping to manage distress. Clinicians will be clinical psychology doctoral students trained in the RISE protocol.

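### The primary time × arm test is not limited to the wait period, so its estimate of the RISE effect depends on unstated time coding and can be diluted; the one randomized contrast should be named as primary.

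*Protocol article*

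**What the plan says.** The Analytic plan (2.1.5.2, Aim 2) sets the main clinical analysis: "Primary analyses will test the time × treatment arm interaction (immediate vs. waitlist) across assessment timepoints using an intention-to-treat framework". The model is described as follows: "Models will include fixed effects for time, treatment arm, and time × arm interactions, relevant covariates, and participant-level random effects". No time coding is given, no subset of visits is named, and no term marks treatment received or crossover.

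Trial design (2.1.1) describes the comparison as "comparing immediate treatment receipt with a 6-week waitlist control condition" and gives the arms different visit schedules:

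- Immediate arm, three assessments: "Participants randomized to immediate treatment will complete assessments at baseline, post-treatment (following completion of UP modules and EW sessions), and 1-week follow-up".
- Waitlist arm, four assessments: "Participants randomized to the waitlist condition will complete assessments at baseline, post-waitlist (i.e., second baseline/prior to treatment initiation), post-treatment, and 1-week follow-up".

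Aim 2 procedures (2.1.3.3) adds that waitlist participants "will then begin RISE within approximately two weeks of the post-waitlist assessment and will follow the same intervention timeline and assessment schedule" as the immediate arm.

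Three places bear on which visits correspond, and they do not fully agree:

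- Aim 2 procedures (2.1.3.3) makes the post-waitlist assessment identical to the immediate arm's post-treatment assessment.
- Aim 2 assessment procedures (2.1.3.4, follow-up assessments) presents it as the equivalent of the immediate arm's 1-week follow-up.
- Study aims (1.7) places the clinical outcomes at post-treatment, a visit that in the waitlist arm falls after RISE.

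**The concern.** Under intention-to-treat a waitlist participant stays coded as waitlist at every visit. At the last two of that arm's four visits the participant has already been offered the full course of RISE. If those visits enter a time × arm interaction, treated observations count as control, and part or all of the interaction compares RISE with RISE.

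The clinical estimates have a stated use. Table 1 (testing phase), the Analytic plan and the Conclusion all say that the results will inform the planning or powering of a definitive trial. Required sample size varies with 1/d², so a planning effect that is halved calls for about (0.50/0.25)² = 4 times as many participants. An estimate near zero could make a promising intervention look inert.

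**Working it through.** The protocol gives no effect size, standard deviation or power for this test, so there is no figure of its own to reproduce. The check asks what the interaction would be expected to show under each plausible time coding.

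**Inputs from the protocol.** There are 30 participants per arm, with the visit schedules above. The immediate arm starts within 2 weeks of randomization, and "Participants will be allowed up to 6 weeks to complete the intervention". If the full 6 weeks are used, its post-treatment visit falls at about week 6 to 8 and its follow-up a week later. The waitlist arm has its post-waitlist visit at week 6, then "Participants in the waitlist condition will then begin RISE within approximately two weeks of the post-waitlist assessment". Its post-treatment visit then falls at about week 12 to 14 and its follow-up at week 13 to 15.

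**Assumptions, not in the protocol.** RISE lowers the outcome by d = 0.5 SD, equally in both arms, and the effect holds at 1 week. Nothing changes while waiting, and there is no dropout. For power: a random-intercept model, intraclass correlation (ICC) 0.3 to 0.7, two-sided 5% level.

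**Expected change from baseline, in visit order.** Immediate: 0, −0.5, −0.5. Waitlist: 0, 0, −0.5, −0.5.

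**(a) Visits matched by name.** Post-treatment: −0.5 − (−0.5) = 0. One-week follow-up: −0.5 − (−0.5) = 0. The post-waitlist visit has no immediate-arm counterpart. This result is 0 for any d, provided that the effect is equal in both arms.

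**(b) Linear visit number.** Slope = Σ(x − x̄)y / Σ(x − x̄)².
- Immediate, x = 0, 1, 2: −0.5/2 = −0.25.
- Waitlist, x = 0, 1, 2, 3: −1.0/5 = −0.20.
- Interaction: −0.25 − (−0.20) = −0.05 SD per visit.

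**(c) Linear weeks.** The same formula is used, and the slope difference is multiplied by the week of the immediate arm's post-treatment visit.

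| Immediate weeks | Waitlist weeks | Slopes | Difference per week | At post-treatment |
|---|---|---|---|---|
| 0, 6, 7 | 0, 6, 14, 15 | −0.0756, −0.0381 | −0.037 | −0.225 |
| 0, 6, 7 | 0, 6, 12, 13 | −0.0756, −0.0437 | −0.032 | −0.191 |
| 0, 8, 9 | 0, 6, 14, 15 | −0.0582, −0.0381 | −0.020 | −0.161 |

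These are illustrative schedules, not bounds. A late immediate start paired with a prompt waitlist start gives (−0.0582 + 0.0437) × 8 = −0.12.

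**(d) Categorical time by visit order.** Visit 2: −0.5 − 0 = −0.50. Visit 3: −0.5 − (−0.5) = 0. Their average is −0.25. The fourth waitlist visit has no counterpart.

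**(e) Baseline and first post-randomization visit only.** −0.5 − 0 = −0.50, with standard error √(2 × 2(1 − ICC)/30) = 0.306, 0.258 and 0.200 at ICC 0.3, 0.5 and 0.7.

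**Approximate power over ICC 0.3 to 0.7:**

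| Coding | Power |
|---|---|
| (b) linear visit number | 7% to 9% |
| (c) linear weeks | 13% to 45% |
| (d) average of visits 2 and 3 | 16% to 30% |
| (d) joint 2-df test | 38% to 74% |
| (e) randomized contrast | 37% to 71% |

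The pilot is not sized for efficacy. The power figures serve only to compare the codings.

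**The case against.** The strongest defence is that the article does not commit to a wrong analysis. It says across assessment timepoints. It does not say all of them, and it does not say how time is coded. The statistical analysis plan could properly settle such details. The article also points toward the right pairing: it calls the post-waitlist visit a second baseline before treatment, and Aim 2 procedures equates it with the immediate arm's post-treatment assessment. With categorical time by visit order, a standard choice, the visit-2 coefficient is intact and the joint test loses essentially nothing against the restricted contrast. Finally, the Power analysis and Limitations sections put feasibility first and ask that effect sizes be read cautiously. No go/no-go rule rests on this interaction, and the article does not say that Hedges' g will be taken from it.

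Most of this stands. A reader might infer that the primary estimate is simply biased toward no effect, or that the trial cannot compare RISE with waiting. The document supports neither reading. The first depends on time coding that is not stated, and the valid contrast exists in the data.

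The defence does not remove the point. The article does state the scope of its primary test, and that scope, unrestricted, conflicts with its own crossover schedule. The passages on visit correspondence do not agree, so an analyst working from visit names could reach the coding that cancels the effect. The emphasis on estimation makes the choice of contrast matter more. The planned sensitivity analyses (completer-only models and unspecified alternatives) do not redefine the primary contrast.

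**Conclusion.** The point holds as an ambiguity with real consequences, at moderate severity. As worded, the primary interaction may include assessments at which both arms have received RISE, and the one randomized contrast is not named. For a true effect of −0.50 SD the expected result runs from 0 (matching by name), through −0.05 SD per visit (linear visit number) and roughly −0.16 to −0.23 SD at post-treatment (linear weeks, the three tabulated schedules), to the full −0.50 in a single coefficient (categorical time, visit 2). The dilution is possible but not inevitable. The figures rest on an equal and persistent effect in both arms, no change while waiting and no dropout; other assumptions would change the sizes. They do not change the fact that the waitlist arm's last two visits are not an untreated control.

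**What to change.** In the Analytic plan (2.1.5.2):

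1. Name as the primary clinical contrast the change from baseline to the first post-randomization assessment: immediate post-treatment against waitlist post-waitlist, with time categorical.
2. Base Hedges' g and its 95% confidence interval on that contrast.
3. Exclude waitlist data after crossover from that model. Report them, with the 1-week follow-up data, separately as uncontrolled within-person change, pooled over arms if wanted.
4. Reconcile Aim 2 procedures (2.1.3.3) with the follow-up paragraph of Aim 2 assessment procedures (2.1.3.4) on which immediate-arm visit the post-waitlist assessment corresponds to, and align the wording in Study aims (1.7).

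The cost is about one paragraph of analysis wording and small edits elsewhere, with no new data or participants. Aim 2 recruitment is anticipated for August 2026, so the change can be made before Aim 2 outcome data exist.

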##### Aim 2 procedures

2.1.3.3

Following eligibility confirmation through the electronic screening survey and synchronous virtual screening, Aim 2 participants will complete online self-report assessments and virtual clinician-administered assessments. Participants randomized to immediate treatment will complete assessments at baseline, post-treatment (following completion of RISE UP modules and EW sessions), and 1-week follow-up. Participants randomized to the 6-week waitlist condition will complete assessments at baseline, post-waitlist/prior to treatment initiation, post-treatment, and 1-week follow-up (see Fig. 1).

Clinician-administered assessments will include the 30-day Timeline Followback (TLFB) [129] to assess alcohol use quantity and frequency; the Structured Clinical Interview for *DSM-5* (SCID-5) Substance Use Disorders module [130] to characterize current and past alcohol/drug use disorders; and the Clinician-Administered PTSD Scale for *DSM-5* (CAPS-5) [131] to determine at least subthreshold PTSD diagnosis and symptom severity. During the baseline virtual visit, participants will schedule all planned intervention sessions and receive a scheduling handout, email reminders for appointments, and clinician contact information for rescheduling if needed. Participants will receive $50 total for completion of baseline self-report and clinician-administered assessments regardless of condition.

**Randomization.** After completion of the baseline self-report and clinician-administered assessments, Aim 2 participants will be randomized 1:1 (unstratified) using REDCap to either immediate treatment receipt or a 6-week waitlist control condition. Randomization assignments will be accessible only to the project coordinator responsible for scheduling participants into the appropriate study timeline. All other study personnel, including assessors, interventionists, and the Principal Investigator, will interact with participants using study IDs and will not be informed of whether participants were assigned to immediate treatment or waitlist. Interventionists and supervisors will know only when a participant is cleared to begin RISE, regardless of whether that occurs immediately after baseline or after the waitlist period. Clinician assessors conducting outcome evaluations will remain masked to condition assignment.

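### The primary clinical model lets the arms differ at a pre-randomization baseline, which costs precision that a common-baseline or baseline-adjusted model would recover from the same data

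*Protocol article*

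**What the plan says.** Section 2.1.5.2 (Initial Outcome and Descriptive Trend Analyses) sets both the contrast and the model: "Primary analyses will test the time × treatment arm interaction (immediate vs. waitlist) across assessment timepoints using an intention-to-treat framework", and "Models will include fixed effects for time, treatment arm, and time × arm interactions", together with relevant covariates and participant random effects. Linear models are foreseen for roughly normal outcomes and generalized models for counts. On baseline covariates it says only "Baseline variables differing across arms and associated with outcomes may be included as prespecified covariates". Completer-only models and unspecified alternative specifications are listed as sensitivity analyses. On reporting: "We will report standardized effect size estimates (e.g., Hedges’ *g*) with 95% confidence intervals", with the emphasis on estimation.

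Section 2.1.3.3 (Aim 2 procedures) fixes the order of events: "After completion of the baseline self-report and clinician-administered assessments, Aim 2 participants will be randomized 1:1 (unstratified) using REDCap". The comparable post-baseline time point is set under the waitlist condition in the same section: "participants will complete a post-waitlist assessment (i.e., prior-to-treatment assessment) identical to the immediate treatment group's post-treatment assessment". Waitlist participants then start RISE.

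Section 2.1.4 gives the size: "we will target enrollment of 60 participants randomized across two conditions (30 per condition"), and "The target sample incorporates anticipated attrition of approximately 20" percent. It states no SD, effect size or correlation between baseline and follow-up.

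**The concern.** Because baseline precedes randomization, any baseline difference between the arms is chance. A model with baseline as a response and a free arm effect estimates that difference anyway and subtracts all of it from the post-baseline difference. With complete data at two time points and a random intercept, the interaction is exactly the difference in mean change scores. Chance imbalance carries over to follow-up only in proportion to ρ, so subtracting all of it adds noise. A model with one common baseline mean, or with the baseline value as covariate, removes only the part that carries over.

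What is at stake is the width of the reported intervals. The plan makes estimates with 95% intervals its main clinical output and expects about 24 follow-ups per arm.

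**Working it through.** **Inputs from the article.** 60 randomized, 30 per arm; attrition about 20%, so 60 × 0.8 = 48 followed up, 24 per arm. Baseline is taken before randomization. The contrast is baseline to first post-baseline assessment, immediate versus waitlist.

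**Assumptions, not in the article.** Approximately normal outcome; SD = 1 at both times, so results are in SD units; correlation ρ, shown over a range; dropout unrelated to outcome; all 60 baselines used, as the mixed model would do.

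The article gives no precision or power figure for the clinical outcomes, so there is none to reproduce first.

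**Formulas.** Let n = 30 baselines and m = 24 follow-ups per arm.

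- Planned model (free baseline means). In each arm the estimated change is (mean post − ρ × mean baseline among those followed) − (1−ρ) × mean baseline among all. The two parts are independent, so Var = 2[(1−ρ²)/m + (1−ρ)²/n].
- Common baseline mean. The second part cancels between arms, so Var = 2(1−ρ²)/m.
- Proportional reduction = (m/n)(1−ρ) / [(1+ρ) + (m/n)(1−ρ)]. With complete data (m = n) this is (1−ρ)/2.

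**Worked at ρ = 0.5.** Planned: 2(0.75/24 + 0.25/30) = 0.0792, SE 0.281. Common baseline: 2 × 0.75/24 = 0.0625, SE 0.250. The reduction is 1 − 0.0625/0.0792 = 21%. The 48 followed up act as about 48 × 0.0792/0.0625 ≈ 61 would under the planned model.

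| ρ | Planned variance (SE) | Common-baseline variance (SE) | Variance reduction | SE reduction | Variance reduction, complete data |
|---|---|---|---|---|---|
| 0.4 | 0.0940 (0.307) | 0.0700 (0.265) | 25.5% | 13.7% | 30% |
| 0.5 | 0.0792 (0.281) | 0.0625 (0.250) | 21.1% | 11.1% | 25% |
| 0.6 | 0.0640 (0.253) | 0.0533 (0.231) | 16.7% | 8.7% | 20% |
| 0.7 | 0.0485 (0.220) | 0.0425 (0.206) | 12.4% | 6.4% | 15% |
| 0.9 | 0.0165 (0.128) | 0.0158 (0.126) | 4.0% | 2.0% | 5% |

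These formulas treat ρ as known. ANCOVA on the 48 followed up pays a small-sample factor of 1 + 1/(48 − 4) = 1.023. At ρ = 0.5 its variance is 0.0625 × 1.023 = 0.0639, so the reduction is 19% instead of 21%. At ρ = 0.95 the planned variance is 2(0.0975/24 + 0.0025/30) = 0.0083 and the ANCOVA variance is 0.0081 × 1.023 = 0.0083: no gain.

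**Check by simulation.** With complete data (30 per arm, ρ = 0.5), random-intercept fits reproduced the change-score difference to rounding error (about 1e-15). In 4,000 simulated trials per setting, with ρ estimated by REML and 30 baselines and 24 follow-ups per arm, the empirical SDs of the planned and common-baseline estimates were 0.284 and 0.253 at ρ = 0.5 (variance ratio 0.79) and 0.219 and 0.206 at ρ = 0.7 (ratio 0.88). Both agree with the table.

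**Does the covariate wording repair it?** No. It is optional, it is triggered by observed imbalance, and it does not name the baseline outcome. Adding the baseline outcome as a main effect while baseline stays a response also does nothing in complete data, because a covariate that is constant over time cannot alter a within-person contrast. The model structure has to change.

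**The case against.** The strongest reply is that nothing here is wrong. Time, arm and their interaction with participant random effects is a conventional analysis, unbiased over randomization. The trial is a pilot aimed first at feasibility and acceptability, the article asks for clinical estimates to be read cautiously, and no decision rule depends on the width of these intervals. An unseen analysis plan might add detail, and the phrase about relevant covariates leaves some room.

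Much of this stands. It limits the point to efficiency and keeps its importance moderate. It does not dispose of it: the article itself names the terms of the primary model, including the arm effect, so the choice is stated and not deferred.

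Three stronger readings are tempting and are not supported:

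- **That the planned analysis is biased or invalid.** Subtracting the whole chance imbalance over-corrects given the imbalance that happens to arise, but over randomization the estimate is unbiased.
- **That the standard error at ρ = 0.5 falls from 0.289 to 0.250, with 48 participants acting as 64.** The 0.289 is √(2 × 1.00/24), a change-score analysis of completers only. The planned mixed model also uses the baselines of those lost, which gives about 0.281 and an equivalent of about 61.
- **That the gain is unconditional.** It depends on a ρ that the article does not give and fades to almost nothing by about 0.9. The algebra covers approximately normal outcomes only. In a log-link count model the interaction is a ratio of rate ratios, and no size is claimed for it here.

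**Conclusion.** The point holds as a matter of efficiency. The stated model ignores a baseline equality that the order of assessment and randomization guarantees in expectation, and its intervals are wider than they need be. Under the stated assumptions the variance is about 12% to 25% higher-than-necessary when expressed as the share that could be saved for ρ from 0.7 down to 0.4, which is about 6% to 14% of the standard error. The calculation rests on equal SDs, dropout unrelated to outcome, and the two-time-point contrast. The change should be made, because it is simple and serves the plan's own emphasis on estimation, but the planned analysis would not be misleading without it.

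**What to change.** In section 2.1.5.2, state the primary model for each clinical outcome in one of two ways:

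- a constrained longitudinal model with baseline as a response, one common baseline mean, and no arm effect at baseline; or
- an ANCOVA-type model for the post-baseline values with the baseline value of the same outcome as a covariate, included whether or not imbalance is observed.

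Report as the estimate the arm difference at immediate-arm post-treatment versus waitlist post-waitlist, which comes before the waitlist arm receives RISE.

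For count outcomes, put the same common-baseline constraint in the generalized mixed model, or use the baseline count as covariate on a scale that handles zeros, such as log(count + 1).

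The cost is model wording and, for ANCOVA, one degree of freedom. No extra participants, visits or measures are needed. Section 2.1.3.1 anticipates Aim 2 recruitment from August 2026, so on that timetable the wording can be settled before any Aim 2 outcome data exist.
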